## **Dose escalation with SIB to intraprostatic/lymphatic GTV in high risk prostate cancer**

### ***Method***

#### **Study design**

The present study will be performed as a single institute prospective consecutive phase II clinical trial with matched historical controls of dose escalation to intra prostatic tumor and, if eligible, to radiological lymph node metastasis in the pelvis.

Patients are recruited consecutively during their consultation at Cancer Centre, Umeå University Hospital, after given both oral and written patient information and due time for consideration.

All patients included in the present study will receive external radiotherapy (RT) of 2,2 Gy to 77 Gy to the prostate in 35 fractions and pelvic nodal radiotherapy of 1,6 Gy to 56 Gy in 35 fractions. A simultaneous integrated boost (SIB) of 84 Gy in 35 fractions (fractional dose 2,4 Gy) will in addition be delivered to macroscopic tumor in the prostate. In case of radiological suspected metastasis in one or more of the pelvic lymphatic nodes according to PET/CT-scan an additional SIB of 70 Gy in 35 fractions (fractional dose 2 Gy) will be delivered to PET-positive nodules.

At baseline QoL questionnaire and baseline symptoms will be collected after given informed consent. Renewed QoL and symptom scoring will be collected at end of treatment and during follow up. A historical control group of 100 consecutive patients receiving external radiotherapy to prostate/pelvic lymph nodes without dose escalation to the intra prostatic macroscopic tumor will be used to compare PFS, OS, LC and QoL. Matching criteria is T-stadium, pre-treatment PSA and GS.

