#### **Concomitant therapy**

Patients will receive hormonal treatment consisting of neo adjuvant LHRH-analog 3 months before start of treatment and 3 months concomitant with radiotherapy. This will be followed by 6 months of anti androgen treatment. In case of suspected lymph node metastasis, individual duration of adjuvant hormonal treatment according to treating physician is allowed.

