### ***Patients***

86 consecutive patients with high risk prostate cancer at Cancer Centre, Umeå University Hospital planned for external radiotherapy with curative intent that meets the following inclusion criteria and none of the exclusion criteria:

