### **Exclusion:**

- Non MR-safe implants or other contraindication to MRI
- WHO PS>1
- Previous pelvic irradiation
- TURP within 6 months
- IPSS >19
- Metastatic disease in skeleton, parenchymal organs or lymph nodes outside the pelvis
- Kreatinin clearance < 30ml/min according to  
<http://www.fass.se/LIF/produktfakta/kreatinin.jsp>

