### *Functional imaging*

In case of inclusion in the full protocol, patients will be referred to an 11C-acetate PET/MRI in treatment position before onset of neo adjuvant hormonal treatment. Three additional 11C-acetate PET/MRI will be performed; after implantation of fiducial markers, in mid-treatment and six months after end of RT. For patients not included in the parallel prognostic imaging protocol, MRI before hormonal treatment and after implantation of the fiducial markers will be performed for target definition. The slice thickness in the planning treatment series is 2 mm.

For all patients, anatomical series consisting of T2 weighted spin-echo based sequences, a T1 weighted gradient echo sequence with DIXON type fat/water separation and a MR angiography. The functional MRI scans include a diffusion weighted EPI sequence (DWI) and a dynamic contrast enhanced spoiled gradient echo sequence (DCE). The DWI sequence is run using two multiple b-values and is reconstructed to an apparent diffusion coefficient (ADC) map that is used for target delineation. The DCE images are analysed using kinetic models and reconstructed to the parameter images used for target definition. The angiography images are registered to the CT image using a rigid mutual information algorithm. All other MRI series are registered to the CT image set using a landmark registration algorithm, with landmarks defined by the implanted gold fiducial markers visible in the T1 weighted MR image and CT. The anatomical series will be used for target delineation in combination with the primary PET scan and planning CT. The primary DWI, will be used in combination with the PET scans to define a macroscopic intra prostatic tumor volume.

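### The comparison with historical controls is open to confounding: controls are matched on three tumour factors only, and the trial's eligibility criteria are not applied to them

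*Protocol*

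**What the plan says.** The protocol's Study design section describes a "single institute prospective consecutive phase II clinical trial with matched historical controls". The comparator is "A historical control group of 100 consecutive patients receiving external radiotherapy to prostate/pelvic lymph nodes without dose escalation" to the macroscopic tumour in the prostate, and this group "will be used to compare PFS, OS, LC and QoL". On balance between the cohorts it says only: "Matching criteria is T-stadium, pre-treatment PSA and GS". The Statistical methods section adds nothing beyond naming matched historical controls.

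The trial cohort is "86 consecutive patients with high risk prostate cancer" who must pass a list of criteria. The Inclusion section requires a nomogram risk of lymphatic spread above 15%. The Exclusion section removes patients with WHO performance status above 1, IPSS above 19, creatinine clearance below 30 ml/min, or "Metastatic disease in skeleton, parenchymal organs or lymph nodes outside the pelvis".

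Under Concomitant therapy the hormone schedule is fixed, with one exception: "In case of suspected lymph node metastasis, individual duration of adjuvant hormonal treatment according to treating physician is allowed". Under Endpoints, PFS runs from inclusion to PSA progression, death from any cause, or radiological progression. Under Functional imaging, patients in the full protocol have a PET/MRI before hormones, and then: "Three additional 11C-acetate PET/MRI will be performed; after implantation of fiducial markers, in mid-treatment and six months after end of RT". Patients outside the parallel imaging protocol have MRI for target definition instead.

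**The concern.** In a comparison with historical controls, the definition of the control group and the factors balanced or adjusted for do the work that randomisation would otherwise do. Here the trial cohort is filtered by criteria that bear on the endpoint, and the control cohort is described only by its treatment and by being consecutive.

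Two links to PFS are direct. Death from any cause is an event, so performance status, age and comorbidity matter. PSA progression is an event, and hormone treatment suppresses PSA, so a difference in hormone duration can move the event date whatever the boost does. Nodal status is linked to both, since it affects prognosis and is the condition under which the trial allows individual hormone duration. None of these is among the matching factors.

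At stake is whether a difference in the three-year rate, positive or null, can be attributed to the boost.

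**Working it through.** **1. Trial rules against control rules.**

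| Feature | Trial patients | Controls |
|---|---|---|
| T-stage, PSA, Gleason score | recorded | matched |
| Nodal risk above 15% | required | not stated |
| WHO performance status above 1 | excluded | not stated |
| IPSS, renal function limits | applied | not stated |
| Disease outside the pelvis | excluded | not stated |
| Nodal status | pelvic nodes allowed | not matched, not described |
| Hormone duration | fixed, or individual if nodes suspected | not matched, not described |
| Age | above 18 | not matched |
| PET/MRI six months after radiotherapy | full-protocol patients only | not described |

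**2. The plan's own figure.** Power considerations gives 86 patients for a 20% improvement in three-year freedom from relapse, with 80% power and two-sided 0.05. No control rate is given, and whether 20% is absolute or relative is not said, so 86 can be neither confirmed nor refuted. Read as absolute with equal arms, the per-arm size is

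n = [(1.960 × √(2p̄(1−p̄)) + 0.842 × √(p0(1−p0) + p1(1−p1))) / 0.20]².

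At 57% against 77%: (1.960 × 0.6650 + 0.842 × 0.6498) / 0.20 = 9.25, and 9.25² = 85.6, so n = 86. With 86 against 100, n = 86 is reached at about 51% against 71%. Power for +20 points with 86 against 100 is 79.7%, 84.8% and 93.1% at control rates of 50%, 60% and 70%. The size is plausible, but it allows for random error only.

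**3. What a systematic shift would do.** Inputs: n1 = 86 and n2 = 100 from the protocol; control rate p and shift b are assumptions. With no true effect, the trial rate is q = p + b. The chance of a significant result favouring the trial is

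1 − Φ[(1.960 × s0 − b) / s1], where s0 = √(p̄(1−p̄)(1/86 + 1/100)), s1 = √(q(1−q)/86 + p(1−p)/100), and p̄ is the pooled rate.

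- p = 0.60, b = 0.05: p̄ = 0.623, s0 = 0.0713, s1 = 0.0710; (0.1397 − 0.05)/0.0710 = 1.26, giving 10.3%.
- p = 0.60, b = 0.10: p̄ = 0.646, s0 = 0.0703, s1 = 0.0696; (0.1378 − 0.10)/0.0696 = 0.54, giving 29.3%.

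| Shift b | p = 50% | p = 60% | p = 70% |
|---|---|---|---|
| 0 | 2.5% | 2.5% | 2.5% |
| +5 points | 10.0% | 10.3% | 11.4% |
| +10 points | 27.5% | 29.3% | 34.3% |

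The reverse also holds. With a true +20 points, a shift of −5 lowers power from 80-93% to 54-68%, and −10 lowers it to 28-34%.

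**4. Timing of the flowchart's 36-month PET-MRI.** Inclusion is about 3 months before radiotherapy (Flowchart). Treatment is 35 fractions at 5 per week, which is 7 weeks or about 1.6 months (Dose specifications). A scan 36 months after radiotherapy therefore falls about 3 + 1.6 + 36 = 40.6, or roughly 41, months after inclusion. It cannot create an event before three years. For a three-year rate, only the six-month scan is an extra opportunity for detection.

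**The case against.** The strongest reply is that the protocol is silent about the controls rather than wrong about them. They may have been screened, staged and treated much like the trial patients. Residual confounding is a known limit of a declared non-randomised phase II design, and covariate adjustment may be left to a statistical analysis plan that is not shown. Part of this stands: imbalance is uncontrolled, not demonstrated, and nothing in the protocol bars an adjusted analysis. But the control group and its complete list of matching factors are fixed in the protocol itself. Following that text leaves the gap open.

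Three stronger readings are tempting and not supported.

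- A reader might infer that PET/MRI purges the trial arm of extrapelvic disease that remains among controls. The PET/MRI applies only to full-protocol patients, is described for target definition, and is not stated to be the test for the exclusion criterion. Controls' staging is not described.
- A reader might add up a bias in the trial's favour. If 5-15% of controls carried such disease, with three-year PFS of 20% rather than 65%, the shift is 0.05 to 0.15 × 0.45 = 2.3 to 6.8 points. If 25% of trial patients had prolonged hormones that cut relapse from 50% to 25%, it is 0.25 × 0.25 = 6.3 points, for a total of about 8.5 to 13. Every input is invented. The sum treats all 86 patients as PET-staged, assumes no control had prolonged hormones, and omits the opposite effect of extra scans, which can bring progression forward in the trial arm.
- A reader might blame the 36-month scan for three-year events. Its timing rules that out.

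**Conclusion.** The concern holds as one of exposure to confounding. The protocol's rule balances T-stage, PSA and Gleason score. It does not apply the trial's eligibility criteria to controls, and it leaves nodal status, hormone duration, age and performance status free, although PFS counts death and PSA progression. It would go too far to say that the PFS difference is confounded, or that the trial arm is favoured: net direction and size cannot be derived from the document. The false-benefit range of about 10-34% rests on assumed control rates of 50-70%, an assumed shift of 5 to 10 points, no true effect, and a simple comparison of 86 with 100. It shows how sensitive the design is to modest imbalance and does not estimate the bias present.

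**What to change.** In Study design:

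1. Restrict controls to consecutive patients who meet the trial's inclusion and exclusion criteria as far as charts allow. Report any criterion that cannot be checked, for example IPSS.
2. Keep the three matching factors, and also adjust the PFS comparison for age, WHO performance status, nodal status judged by imaging available in both cohorts, and planned hormone duration.
3. Add a sensitivity analysis in node-negative patients on fixed-duration hormones in both cohorts.
4. Add a sensitivity analysis that does not count progression found only on the six-month research PET/MRI.
5. Do not use treatment year as a covariate. With historical controls it nearly determines the arm, so an adjusted model would have to extrapolate. Report the calendar periods of both cohorts and state era differences as a limitation.

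These choices should be fixed before outcomes are compared, since covariates chosen afterwards invite selective adjustment. Replacing matching by propensity weighting is a matter of preference and is not needed. The cost is a chart review, replacement of some controls by the next eligible consecutive patients, and slightly wider confidence intervals. No treatment or visit changes.

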#### **Trial period**

Patient recruitment is calculated to take 18 months and follow-up time 60 months

#### **Concomitant therapy**

Patients will receive hormonal treatment consisting of neo adjuvant LHRH-analog 3 months before start of treatment and 3 months concomitant with radiotherapy. This will be followed by 6 months of anti androgen treatment. In case of suspected lymph node metastasis, individual duration of adjuvant hormonal treatment according to treating physician is allowed.

### ***Patients***

86 consecutive patients with high risk prostate cancer at Cancer Centre, Umeå University Hospital planned for external radiotherapy with curative intent that meets the following inclusion criteria and none of the exclusion criteria:

### **Inclusion:**

- Histologically confirmed high risk prostate cancer with a risk of lymphatic spread >15% according to the MSKCC nomogram (1), previously untreated  
<http://nomograms.mskcc.org/Prostate/PreTreatment.aspx>
- Written informed consent
- > 18 years
- Fiducial gold markers implanted in the prostate (min 3)

### **Exclusion:**

- Non MR-safe implants or other contraindication to MRI
- WHO PS>1
- Previous pelvic irradiation
- TURP within 6 months
- IPSS >19
- Metastatic disease in skeleton, parenchymal organs or lymph nodes outside the pelvis
- Kreatinin clearance < 30ml/min according to  
<http://www.fass.se/LIF/produktfakta/kreatinin.jsp>

## ***Radiation treatment***

### **Radiotherapy**

The RT will be delivered with treatment position and fixation according to standard practice of the department. Treatment technique used will be volumetric modulated arc therapy (VMAT) to utilise the benefits of intensity modulated radiation therapy (IMRT) in dose distribution (2-6) and the benefits of VMAT in shortend treatment time (7)

The time limit specified for this protocol from set up portal imaging until end of treatment will be <7 minutes. A review of our previous in house treatment times, from portal imaging until beam off, in our prostate/pelvic nodal VMAT treatments have been performed prior to this study. In 80% of the treatment fractions the treatment time was equal to or less than 7 min. In light of this we consider a margin of 2 mm sufficient for the intra fractional movements of the prostate (7).

A daily online position verification protocol with implanted fiducial markers will be used to minimize positioning errors (8).

The target volume of pelvic lymph nodes is based on the vascular structures of the pelvis according to the RTOG consensus (9). The standard deviations at our treatment centre for prostate/pelvic nodal VMAT treatments with the same pelvic target definitions (Sigma) regarding fiducial markers vs bony structures is 0,5 mm, 1,8 mm and 1,5 mm respectively for lateral, longitudinal and vertical shifts whereas the mean random error (sigma) is 1,2 mm, 2,6 mm and 2,4 mm respectively for lateral, longitudinal and vertical shifts (outliers subtracted from analysis). This will require an additional margin of 7 mm for the PTV-PNV as we position only on the intra prostatic fiducial markers.

At minimum, once a week a cone beam CT on the treatment machine will be performed in order to assess the relation between skeletal/vascular structures and prostate compared to the CT used for dose planning to identity outliers. The action level for treating

physician/investigator to evaluate if a correction of the pelvic radiation volume, e.g. increase the margin, or extra imaging is necessary is a 7 mm deviation from set up exam.

Separate instructions (oral and written) are given to the patients in order to minimise bowel movements and variations in rectal and bladder filling at the visit before the start of RT.

## **Patient data acquisition**

For all patients, a CT based simulation with 2 mm slice thickness shall be made after implantation of fiducial markers in treatment position. In patients with rectum > 4 cm due to faeces or gas, new planning CT and MRI should be performed prior to treatment planning. The bladder should be comfortably filled.

CT images will be obtained from the lower lumbal spine to 10 mm below the tuberositas ischii.

### *Functional imaging*

In case of inclusion in the full protocol, patients will be referred to an 11C-acetate PET/MRI in treatment position before onset of neo adjuvant hormonal treatment. Three additional 11C-acetate PET/MRI will be performed; after implantation of fiducial markers, in mid-treatment and six months after end of RT. For patients not included in the parallel prognostic imaging protocol, MRI before hormonal treatment and after implantation of the fiducial markers will be performed for target definition. The slice thickness in the planning treatment series is 2 mm.

For all patients, anatomical series consisting of T2 weighted spin-echo based sequences, a T1 weighted gradient echo sequence with DIXON type fat/water separation and a MR angiography. The functional MRI scans include a diffusion weighted EPI sequence (DWI) and a dynamic contrast enhanced spoiled gradient echo sequence (DCE). The DWI sequence is run using two multiple b-values and is reconstructed to an apparent diffusion coefficient (ADC) map that is used for target delineation. The DCE images are analysed using kinetic models and reconstructed to the parameter images used for target definition. The angiography images are registered to the CT image using a rigid mutual information algorithm. All other MRI series are registered to the CT image set using a landmark registration algorithm, with landmarks defined by the implanted gold fiducial markers visible in the T1 weighted MR image and CT. The anatomical series will be used for target delineation in combination with the primary PET scan and planning CT. The primary DWI, will be used in combination with the PET scans to define a macroscopic intra prostatic tumor volume.

## **VOI-definition**

The definition of volumes follows the recommendations made by ICRU in Report 50, 62 and 83 for photon beam therapy (10, 11). Naming of VOI according to national standard adopted from ICRU by SSM 2014:25.

### *Target volumes*

#### **Gross tumor volume intra prostatic, GTVT:**

Outlined on the DWI combined with information from the other MRI series, the primary PET scan and histological report, clinical judgment of treating physician with consultant of investigator/radiologist if needed will be used.

#### **Gross tumor volume metastatic lymph node, GTVN1,2..:**

Any lymph nodes suspected for macroscopic tumor growth in the primary PET/MRI are to be outlined on the planning CT.

#### **Clinical target volume prostate, CTVT:**

The entire prostate including proximal seminal vesicles outlined in CT (with anatomical MR support). Any areas with uncertainties regarding extra capsular growth or tumor invasion in vesicles are to be included.

**Clinical target volume vesicula seminalis, CTVT2:**

The seminal vesicles outlined on CT (with anatomical MR support) without margin.

**Clinical target volume pelvic lymph nodes, CTVN:**

The vessels, arterial and vein, will be outlined on CT (with angio sequence MR support) and include bilaterally with a margin of 7 mm in all directions (adjusted for bowel, bladder, bone and muscle): distal common iliac, presacral (S1-S3), external- and internal iliac and the obturator vascular structures. Bony landmarks are L5/S1 interspace (cranial) and superior aspect of the pubic bone (caudal). If applicable, GTVN shall be included in CTVN.

**Planning target volume intra prostatic tumor, PTVT\_84**

An isotrop margin of 2 mm will be added around GTV adjusted so that no part of PTVT\_84 extends into urethra, bladder or rectum/anal canal.

**Planning target volume prostate, PTVT\_77**

Consists of CTVT and an isotrop margin of 6 mm.

**Planning target volume metastatic lymph node, PTVN1,2..\_70\_:**

GTVN\_1,2.. with a margin of 7 mm in all directions if applicable.

**Planning target volume pelvic lymph node, vesicula seminalis, PTV\_56**

Consists of CTVT2 and CTVN with a margin of 7 mm in all directions.

**Note!**

If automatic margin expansion is used, check the margin in the cranio-caudal (cc) direction.

Delineation of treatment volumes may be performed by treating physician, however it is recommended that treatment plan is approved by investigator before start of treatment.

**Organ at risk**

**Rectum and AnalCanal**

The rectal volume shall be outlined as the outer contour of the rectum, i.e. including the rectal wall. The extension of the segmentation shall, if applicable, be 5 cm in the cranial direction from the centre of the prostate and in the caudal direction down to and including the anus. , adjusted to 10 cm cranially-caudally. The anal canal shall be outlined as a separate OR consisting of the most caudal 4 cm of the rectum.

**BowelBag**

The potential space for the bowel should be outlined as possible OAR. Borders are the abdominal wall anteriorly, pelvic sidewalls laterally (excluding the pelvic lymph nodes), superiorly to one slice above the last image where the lymph nodes are outlined and the inferior margins goes to the top of the CTV-P on the side of the bladder for the part of the bowel that may fall down there.

**Bladder**

The entire bladder from neck to dome, including the bladder wall

**Urethra**

Outlined as a tube with a diameter of 3mm, cranially from the neck of the bladder stretching the whole length of the PTV-P caudally, it is recommended to approximate the urethra in sagittal series initially.

**FemoralHead\_L/R**

Without margin

**PenileBulb**

The penile bulb shall be outlined on the CT images (MR guidance is recommended).

## Dose specifications

Prescribed average dose to CTVT: 2,2 Gy to 77 Gy, 5 fractions per week with a total of 35 fractions.

Prescribed average dose to CTV2 and CTVN: 1,6 Gy to 56 Gy in 35 fractions.

Prescribed average dose to GTV: 2,4 Gy to 84 Gy in 35 fractions.

Prescribed average dose to GTVN1,2...: 2Gy to 70 Gy in 35 fractions.

## Dose-volume objectives

If not otherwise specified, prescribed dose refers to CTVT.

| Priority | VOI         | D-V objective                                                                                                |                                                                                                                       |
|----------|-------------|--------------------------------------------------------------------------------------------------------------|-----------------------------------------------------------------------------------------------------------------------|
| 1        | CTVT        | $D_{98\%} \geq 74.7 \text{ Gy}$                                                                              | The “near minimum dose” to CTVT shall be greater than or equal to 97% of the prescribed dose.                         |
| 2        | PTVT_77     | $V_{73\text{Gy}} \geq 95\%$                                                                                  | The 95% isodose shall cover at least 95% of PTV_77.                                                                   |
| 3        | Rectum      | $V_{69\text{Gy}} \leq 15\%$                                                                                  | Less than 15 % of the outlined rectal volume should receive doses greater than 90% of the prescribed dose.            |
| 4        | PTVT_77     | $D_{98\%} \geq 70 \text{ Gy}$                                                                                | The “near minimum dose” to PTV_77 should be greater than or equal to 95% of the prescribed dose.                      |
| 5        | Rectum      | $V_{58\text{Gy}} \leq 35\%$                                                                                  | Less than 35 % of the outlined rectal volume should receive doses greater than 75% of the prescribed dose.            |
| 6        | FemoralHead | $D_{2\%} \leq 54 \text{ Gy}$                                                                                 | The “near maximum dose” to the femoral heads should be less than or equal to 70% of the prescribed dose.              |
| 7        | BowelBag    | $V_{45\text{Gy}} \leq 150\text{cc}$
$V_{30\text{Gy}} \leq 300\text{cc}$
$D_{2\%} \leq 53.2 \text{ Gy}$ | The “near maximum dose” to the bowel bag should be no more than 95% of the prescribed dose CTVT and N.                |
| 8        | Urethra     | $D_{2\%} \leq 77 \text{ Gy}$                                                                                 | The “near maximum dose” to the urethra should be less than or equal to the prescribed dose.                           |
| 9        | PTV_56      | $V_{53\text{Gy}} \geq 95\%$                                                                                  | The 95% isodose should cover at least 95% of CTVT and N.                                                              |
| 11       | Body        | $D_{2\%} \leq 81.9\%$                                                                                        | The global “near maximum dose” outside of PTVT_84 should be less than or equal to 105% of the prescribed dose. |

|    |         |                      |                                                                          |
|----|---------|----------------------|--------------------------------------------------------------------------|
| 12 | Bladder | $D_{mean} \leq 61,5$ | Mean dose to bladder should be less or equal to 80 % of prescribed dose. |
|----|---------|----------------------|--------------------------------------------------------------------------|

